# Implementing an online-delivered exercise program for childhood cancer survivors: A hybrid effectiveness-implementation protocol for the MERRIER study

**DOI:** 10.1016/j.jsampl.2025.100095

**Published:** 2025-03-12

**Keywords:** Childhood cancer, Paediatric oncology, Exercise, Physical activity, Fitness, Digital health

## Abstract

**Background:**

Physical activity levels are low in childhood cancer survivors. Structured physical activity programs are not routinely provided, despite being safe and beneficial for improving physical and psychological health. Innovative health promotion programs delivered online may allow families to receive equitable health support, which may foster survivors to improve their health.

**Aims:**

To determine implementation factors of an online exercise program recruited through a community organization, and effectiveness on physical activity levels and self-efficacy for childhood cancer survivors.

**Methods and analysis:**

The MERRIER study is a type-1 hybrid effectiveness-implementation. Sixty children (5–18 years old) who have completed treatment for any cancer type will be enrolled between March 2025 and June 2026. Participants will be randomised (stratified by age, cancer type and sex) 1:1 to 3-months multimodal exercise or control group. The intervention group will receive five online consultations with an Accredited Exercise Physiologist to provide behaviour counselling, and prescribe an individualised aerobic, resistance and balance exercise program at low-moderate intensity. The RE-AIM framework will assess reach (e.g. recruitment rate), effectiveness (e.g. physical activity levels), adoption (e.g. qualitative interviews), implementation (e.g. exercise adherence), and maintenance (e.g. self-efficacy at follow-up). Physical function and patient-reported outcomes will be assessed at baseline (T0), post-intervention (T1; week 12) and follow-up (T2, week 24). An Axivity AX3 accelerometer will measure physical activity over five-days at T0/T1.

**Implications:**

If effective, we aim to collaborate with community organisations, who are well placed to implement similar programs to childhood cancer survivors.

**Ethics:**

The study was approved by The University of Sydney Health Research Ethics Committee (2024/HE000391).

**Trial registration:**

ACTRN12624000604505p.

Key points
-This is the first study to investigate the implementation and delivery of an online exercise program to childhood cancer survivors in conjunction with a community organisation.-Children aged 5–18 will be provided with individualised exercise programs based on their needs, preferences and abilities.-If successful, this online program could be an equitable option to deliver programs to children, which is particularly useful to families who live far from specialised services.

## Introduction

1

The survival rate of childhood cancer is improving due to improved treatment protocols and supportive care [1,2]. However, the cost of cure is high, with most survivors experiencing lifelong chronic conditions [3]. Treatment protocols for paediatric oncology often include therapies such as anthracycline, methotrexate, vincristine, steroids and thoracic radiation [1]. These therapies can increase risks of conditions such as cardiovascular disease, diabetes, obesity, osteoporosis, mental health disorders and secondary cancers [4]. Yet, though childhood cancer survivors have increased risk for several chronic conditions they also are less likely to engage in physical activity and have lower fitness than their same aged peers [2,5] further increasing their risk and burden caused by these conditions.

Participating in regular physical activity and exercise can improve fitness, muscle strength, metabolic health, bone density, fatigue, mental health and quality of life for children impacted by cancer [2,[6], [7], [8]]. Participating in regular exercise has also demonstrated to reduce the risk of cardiovascular, metabolic, and psychological adverse and late-effects of childhood cancer treatment [9,10]. Recent international paediatric oncology exercise guidelines [11] called for exercise and physical activity to be promoted across all key settings of childhood cancer survivors’ lives, including hospitals, homes, schools and communities. Despite these benefits and guidelines, most childhood cancer survivors participate in less physical activity than their peers [12] and may benefit from physical activity support. It is particularly important to establish healthy behaviours in childhood [13], it is crucial to support, motivate and educate childhood cancer survivors to become active to maintain their health and reduce the risk of developing chronic conditions [3].

Identifying and overcoming barriers to implementing exercise and physical activity programs into care is an important next step to improve short and long-term physical and psychological health of childhood cancer survivors [14]. Several barriers prevent childhood cancer survivors from receiving physical activity programs. Families may experience practical barriers such as not living locally to specialised services, lack awareness of the benefits, or have financial constraints [15,16]. Healthcare providers may be a facilitator or barrier in motivating patients to become physically active [15]. Organizational barriers including time and staff resources, and lack of established referral pathways have been identified as key barriers to implementing exercise programs in oncology [17,18]. In Australia, while some oncology multi-disciplinary teams include exercise professionals such as Accredited Exercise Physiologists (AEP) and physiotherapists, a lack of widespread implementation means that not all patients can be supported [19].

Physiotherapists (also termed physical therapists) and AEPs (also termed certified exercise physiologists, kinesiologists) are well-suited exercise professionals to provide assessments, advice, programs and self-management on exercise. These allied health professionals may play an important role in engaging childhood cancer survivors in physical activity and coaching them to obtain the tools to self-motivate themselves. Exercise programs can be individualised for childhood cancer survivors based on physical ability, needs, exercise history and preferences to ensure adequate adherence. Given the heterogeneity and health challenges the childhood cancer population experience, the MERRIER study has been developed to support these children engage in tailored physical activity programs and build their self-efficacy.

There is growing recognition among families of childhood cancer patients and healthcare providers to access programs to support physical recovery after treatment, to address their unique physical and psychosocial challenges. In an Australian study, among 64 parents of childhood cancer survivors who received an exercise physiology consultation, 97 ​% felt that future children with cancer would benefit from an assessment by an AEP [20]. In Australia, the publicly funded Medicare system allows eligible people with a chronic condition to receive up to five subsidized consultations per year with AEPs or physiotherapists. Despite potential benefits, there are challenges to delivering assessment and supports from AEPs and physiotherapists due to scheduling and geographic constraints [21]. This has created the need to connect with families in innovative ways, such as using online and remote digital health services and connecting with local community organisations. Recent studies have demonstrated the validity of performing remote physical assessments online in teenagers and young adults with and without mobility disabilities [22], which is useful in countries like Australia where patient populations often live far from specialised services [21]. Additionally, delivering exercise support programs using online platforms has been demonstrated to be feasible in childhood cancer survivors, and able to achieve acceptable program adherence [7]. While there are remotely delivered exercise trials in progress among young adult survivors of childhood cancer (aged 18–39 years) [23], there are limited studies conducted in children and adolescents aged 5–18 years. Additionally, there are limited paediatric exercise oncology studies simultaneously evaluating the effectiveness of exercise while identifying barriers and facilitators to its implementation [24].

### Aims

1.1

This trial is a type 1 hybrid effectiveness-implementation trial designed to:1)Determine the effectiveness of the MERRIER intervention, an exercise program delivered online to childhood cancer survivors in conjunction with a community organisation, in improving moderate-vigorous physical activity levels and physical activity self-efficacy.2)Examine the factors that may increase the program reach, effectiveness, adoption, implementation and maintenance

## Methods and analysis

2

### Design and setting

2.1

A mixed methods type 1 hybrid effectiveness-implementation randomised trial design will be used to evaluate the preliminary effectiveness and implementation of the “Maximizing Exercise, Resilience, and Implementation to Empower Recovery – An Online Intervention for Increasing Physical Activity and Self-Efficacy in Childhood Cancer Survivors” (MERRIER) study (ANZCTR Trial Registration #ACTRN12624000604505p) [25]. The MERRIER study will be delivered by researchers with recruitment facilitated by a childhood cancer community organisation (e.g. Camp Quality).

### Participants and screening

2.2

Recruitment is planned between March 2025 and June 2026. Eligibility criteria for participants include those: aged 5–18 years, diagnosed with any cancer type, completed intensive treatment (e.g. intravenous chemotherapy, stem cell transplant, radiation therapy, however maintenance therapy is permitted). Participants and a parent/guardian must have sufficient English proficiency to understand the consent process and exercise intervention. Translation services are available for participants who speak supported languages, as specified by service availability. Exclusion criteria include having a medical condition that would prohibit exercise participation at discretion of the research team and if needed in consultation with treating doctor (e.g. but not limited to cardiomyopathy, uncontrolled cardiac arrhythmias), and pregnant females.

Parents of potential participants will be informed of the opportunity to participate by the community organisation staff. Parents/guardians of eligible participants will be provided with the study information sheet and consent form to consider permitting their child to participate. Families from outside community organisations are permitted to enrol. Parents will then discuss the study in more detail with the lead investigator (DM) prior to providing informed consent. Consent forms and study data will be then collected and managed by the research team using Research Electronic Data Capture (REDCap) [26], who will then become the point of contact for the study. After providing informed consent, information will be gathered about cancer-related medical history, treatment-related side effects, other chronic conditions or injuries, and physical activity readiness and risk-management via the Pre-Exercise Screening System for Young People (PSS-YP) [27]. The intake form and PSS-YP will be reviewed by the lead investigator (DM), who is an Accredited Exercise Physiologist accredited with Exercise and Sports Science Australia, to conduct a safety screen for exercise participation.

### Randomization

2.3

Following the completion of baseline (T0) assessments including physical assessments, questionnaires and 5-day objective physical activity wrist-worn accelerometry, participants will be assigned to either the exercise intervention or control group (Fig. 1). Randomization will occur in a 1:1 ratio using the online computer-generated randomisation software, Sealed Envelope, which will be completed by an independent researcher outside the core study team. Randomisation will be performed in blocks to ensure balance across important variables, including age (categorized into three groups: 5–9, 10–13, and 14–18), sex (male, female), and disease type (liquid, solid, brain tumours).

**Fig. 1 fig1:**
[figure not shown]
Flow chart of study procedures.

### Outcome measures

2.4

Outcome measures are presented in Table 1, and will be completed at three time points: (1) baseline (T0; week 0); (2) post-intervention (T1; week 12); and (3) follow-up (T2; week 24). Physical assessments are conducted online using Microsoft Teams by an AEP in the research team. Patient-reported outcomes (PROs) questionnaires will be emailed to each participant's parent/guardian at all time points via REDCap. Accelerometers will be mailed to participants to be worn for 5-days at the baseline (T0) and post-intervention (T1) timepoints.

**Table 1 tbl1:** Summary of study timepoints and procedures.

	Baseline (Week 0)	Post-intervention (Week 12)	Follow-Up (Week 24)
**Accelerometer:** Physical activity level (wrist-worn accelerometer for 5-days)	x	x	

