### Physical fitness outcomes

2.5

Physical fitness assessments will be conducted online using Microsoft Teams at each time point, and will take approximately 20–30 ​min, with results recorded in REDCap. All assessors will be trained in the assessment protocol, with the lead researcher having paediatric exercise oncology experience. Assessors will send videos of each assessment prior to the session, and then explain and demonstrate each assessment prior to the participants’ attempt. The researcher will record the results and supervise participants, in addition to having a parent or guardian supervising them in person, unless mutually agreed that parent supervision is not required (for adolescent participants). The physical fitness assessments (Table 1) include the following validated assessments.

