#### Sit and reach

2.5.6

Sit and reach test is a measure of flexibility of the lower back and hamstring muscles, which has been extensively used and validated in childhood populations [34]. This test involves sitting on the floor with legs stretched out straight ahead. The participant holds that position for at least 2 ​s while the distance is recorded by their parent/guardian. Touching the toes equals the baseline (0 ​cm), with any performance past the toes indicating a positive score in cm, and not reaching the toes indicates a negative score in cm. Participants will be provided with a ruler to measure the distance from the toes.

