### Exercise intervention

2.8

The five exercise consultations are conducted online using Microsoft teams, and the exercise prescription is delivered remotely to participants using Physitrack (Physitrack Limited) exercise prescription software (available to participants as a website or digital application). Within two weeks of the baseline assessment, participants randomized to the intervention will receive the first of five telehealth consultations with an AEP (Fig. 1) over 3 months to develop and go through an exercise program individualised to their needs, physical activity levels, barriers, preferences and goals. The program will be designed with the purpose of participants utilising themselves, and/or with their family, peers, community sport and at school. Participants will be mailed simple exercise equipment to use at home for their program based on their preferences and needs such as resistance bands, skipping ropes and provided with a $50 (AUD) voucher to use on sport or physical activity equipment. The MERRIER exercise intervention is guided by exercise guidelines in childhood cancer [11], previous research (e.g. PICASSO Study [20] and the CanMOVE study which also adopts a flexible exercise prescription approach during the treatment phase for childhood cancer [42]), as well as the RePlay theoretical model for structured active play [43], and was co-designed with oncology health professionals, and childhood cancer survivors and their parents. The number of supervised consultations in the study (five) was selected to be in line with the number of government subsidised (Medicare) sessions with an AEP or physiotherapist available each year to Australians with a chronic condition.

During each consultation with the AEP, participants will discuss any challenges with the program, and adjustments will be made. The second component of each consultation is completing each prescribed exercise together, allowing for technique adjustments and questions. Where required, participants will be offered strategies on increasing their physical activity participation in line with the paediatric oncology exercise guidelines [11]. Physical activity programs will be structured and individualised based on the framework in Table 2.

**Table 2 tbl2:** Framework for structure of exercise physiology consultations and factors for exercise prescription.

Exercise Guidelines	**Duration:** Education on paediatric oncology physical activity guidelines (“Move when you can”) [11]

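### Nothing in sections 2.4 and 2.5 masks the assessor of the video fitness tests or separates that assessor from the child's coach, and a parent who knows the arm records sit-and-reach, so these secondary outcomes are open to assessor bias at T1 and T2

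*Protocol article*

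**What the plan says.** All references are to the protocol article.

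- **Who tests.** Section 2.4: "Physical assessments are conducted online using Microsoft Teams by an AEP in the research team". Section 2.5 adds: "The researcher will record the results and supervise participants, in addition to having a parent or guardian supervising them in person".
- **Safeguard.** Section 2.5: "All assessors will be trained in the assessment protocol, with the lead researcher having paediatric exercise oncology experience". Neither blinding nor independence of assessors is mentioned anywhere.
- **Who coaches.** Section 2.8: "participants randomized to the intervention will receive the first of five telehealth consultations with an AEP". Section 2.1: "The MERRIER study will be delivered by researchers with recruitment facilitated by a childhood cancer community organisation".
- **Sit-and-reach.** Section 2.5.6 has the child hold the position "while the distance is recorded by their parent/guardian".
- **Timing.** Section 2.3 places randomisation after the T0 assessments and gives it to someone outside the core team. The T0 tests therefore precede allocation, and the T1 and T2 tests follow it.
- **Status.** Section 2.11 lists the physical assessments among the secondary effectiveness outcomes. The co-primaries are self-efficacy and accelerometer-measured activity.

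**The concern.** The fitness tests need an observer's judgement, the child's effort, or both. Someone decides over video whether a sit-to-stand or push-up counts, whether the thigh came high enough in the step test, when single-leg balance was lost, and when to stop the watch in the timed up-and-go. An observer who knows the arm can score or encourage more generously without meaning to. The risk is greater if that observer has also coached the child for three months. Table 2 allows consultation goals to include assessment performance, so the coach may have an interest in the result.

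For sit-and-reach, the parent can hardly be unaware of the arm. Intervention families receive consultations, mailed equipment and a voucher (section 2.8), whereas control families receive emailed resources (section 2.10).

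At stake is the between-arm comparison of fitness after allocation. Section 3 says the findings will inform whether remote delivery improves fitness, among other things. Randomisation and the mixed models of section 2.14 do not remove a measurement difference that arises by arm after allocation.

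**Working it through.** **Step 1. Passages side by side.**

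| Question | What the article fixes | What it leaves open |
|---|---|---|
| Who scores at T1 and T2? | An AEP in the research team (2.4) | Whether that AEP coached the child |
| Who coaches? | An AEP (2.8); researchers deliver the study (2.1) | Whether that AEP also tests the child |
| Does the assessor know the arm? | Nothing stated; training only (2.5) | Masking |
| Who records sit-and-reach? | The parent or guardian (2.5.6) | Whether the assessor checks the value |

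Followed as written, the plan permits an unmasked assessor for every test and permits that assessor to be the child's coach. For sit-and-reach, recording by an unmasked person is prescribed.

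**Step 2. The plan's own sample size (2.13), for the number of evaluable children.** Inputs: difference 10 min/day, SD 11 min/day, 90% power, p < 0.05 (taken as two-sided), 1:1 allocation, 15% drop-out, 60 enrolled.

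- n per arm = 2 × (1.960 + 1.282)² × (11/10)² = 2 × 10.51 × 1.21 = 25.4, rounded up to 26, so 52 in total. This matches the plan.
- Evaluable after drop-out: 60 × 0.85 = 51, or 25.5 per arm. Power on the accelerometer outcome is then 0.901.

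This calculation concerns an outcome that no AEP scores, so it stands whatever happens to the fitness tests.

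**Step 3. Illustration of size.** The documents give no bias and no SD for any fitness test. The following are assumptions: a systematic bias b, in SD units, in favour of one arm; a true difference of zero; the same 15% loss for the fitness tests; and a two-sided 5% z-test comparing scores at one time point.

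- SE = √(2/25.5) = 0.280 SD
- Shift s = b / 0.280
- False-positive rate = P(Z > 1.96 − s) + P(Z < −1.96 − s)

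| Assumed bias b | Shift s | Upper tail | Lower tail | False-positive rate |
|---|---|---|---|---|
| 0 | 0 | 0.025 | 0.025 | 5% |
| 0.1 SD | 0.357 | 0.054 | 0.010 | 6.5% |
| 0.2 SD | 0.714 | 0.106 | 0.004 | 11% |
| 0.3 SD | 1.071 | 0.187 | 0.001 | 19% |

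For a sense of scale only: if the sit-to-stand SD were 4 repetitions (also an assumption), 0.1 to 0.3 SD would be 0.4 to 1.2 repetitions credited on average across one arm. The estimated effect itself moves by the whole of b at any sample size.

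**The case against.** The strongest reply is that this argues from silence in a condensed article. Sections 2.4 and 2.8 each say an AEP, not the same AEP. Fig. 1 is not shown, and the full protocol may contain a rule on who tests whom. The article also standardises the tests: instruction videos and demonstrations beforehand, the same push-up type throughout, fixed time windows, a supplied rope and ruler, and two timed up-and-go trials averaged. The co-primaries are not scored by an AEP, and section 2.1 speaks of preliminary effectiveness.

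Much of this stands. A reader might infer that intervention children are tested by their own coach and control children by someone they barely know. The documents do not support that: they allow the overlap but do not say it happens. A reader might also infer that the team has several assessors ready to swap. Section 2.5 uses the plural, which implies more than one, but gives no number, and the only individual identified as an AEP is the lead investigator (2.2). Nor is every scoring rule loose: in the balance test the arm criterion and the 30 s limit are concrete, and judgement enters mainly through the legs. At the low end of the assumed range the false-positive rate is close to nominal.

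The reply does not dispose of the point. The article does not leave outcome assessment to another document. It names the assessor and the safeguard, and the safeguard is training, which standardises but does not mask. Section 2.5.6 states the parent's role outright. Even with no coach–assessor overlap, nothing keeps a team AEP unaware of the arm.

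**Conclusion.** The point holds in a limited form. As written, the fitness tests at T1 and T2 are unmasked, coach–assessor overlap is permitted though not confirmed, and sit-and-reach is recorded by someone who will know the arm. Only secondary outcomes are affected. The accelerometer co-primary and the sample size of 52 evaluable and 60 enrolled are untouched.

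The size of any bias is unknown. Under assumed biases of 0.1 to 0.3 SD and about 51 evaluable children, the 5% false-positive rate on a single fitness test becomes about 6.5% to 19%. These figures show sensitivity; they do not predict what will happen in this trial. The change is worth making because it is cheap and the exposure cannot be corrected in the analysis.

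**What to change.** **Section 2.4.** State that the T1 and T2 tests are done by an existing trained assessor who did not deliver that child's consultations and is not told the allocation. Use the same scripted encouragement for every child, and ask families not to disclose the arm.

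**Section 2.5.6.** Have the parent hold the ruler while the assessor reads or confirms the value on camera. Confirmation is the safer wording, because the article does not show that a ruler can always be read over a family's webcam.

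**Fallback.** Where staffing does not allow a swap, report the fitness outcomes as unblinded and interpret them accordingly.

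**Cost.** A scheduling rule, a short script and a change to one test instruction, with no added visit or test. The downside is less scheduling flexibility and some accidental unmasking. Whether it needs no extra staff depends on how many trained assessors there are, which the article does not say.
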